**Methods:**

A randomized, double-blind, sham-controlled, full-factorial design will be conducted. The effects of transcranial direct current stimulation (tDCS) and intermittent theta-burst stimulation (iTBS) will be investigated over four different sessions (sham tDCS + sham iTBS, anodal tDCS + sham iTBS, anodal tDCS + active iTBS and sham tDCS + active iTBS) in 30 healthy adult volunteers. A 99mTc-ethylene cysteine dimer (99mTC-ECD) will be administered during the NIBS session and neuroimaging will be acquired within one hour. Salivary cortisol will be collected before and after each session and an n-back working memory task will be applied after the end of each NIBS session. The outcomes will be cerebral perfusion alterations (99mTC-ECD SPECT), accuracy and reaction time in the n-back task, and changes in salivary cortisol level.

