Before the start of each of the four experimental sessions, participants will be asked to answer a few baseline measurements such as the HAMD, BDI, PANAS, and Hamilton Anxiety Inventory (HAI) and a visual analogue scale (VAS). These will essentially be applied to identify participants’ brain state before the NIBS session and can also serve as potential moderators of the NIBS effects. Afterward, the volunteers’ resting motor threshold^32^ will be determined using a MagVenture device (MagPro X100, Denmark) and a figure of eight coil. Salivary cortisol will be collected after the motor threshold measurement and before venous access is obtained for administration of the 99mTc-ECD radiotracer. After venous access, subjects will undergo a neurostimulation session ( Figure 1A ). First, the tDCS device will be switched on. The tDCS session will last 20 minutes. However, the tDCS protocol will be applied alone for the first eleven minutes and then, for the last 9 minutes of the neurostimulation session, the iTBS protocol over the left DLPFC will be applied concomitantly. The radiotracer (99mTC-ECD) will be injected right after the start of the iTBS protocol ( Figure 1B ).

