**Figure 1 f01:**
[figure not shown]
Protocol that will be applied. A) Sequence of the data acquisition and group allocation. B) Noninvasive brain stimulation protocol. atDCS = anodal transcranial direct current stimulation; AE = adverse effects; iTBS = intermittent Theta-burst stimulation; min = minutes; MRI = magnetic resonance imaging; SPECT = single photon emission computed tomography.

VAS and salivary cortisol will be collected immediately after the end of the session. For the VAS scale, participants will be asked to manually indicate on horizontal 10 cm lines whether they are experiencing any current pain. ‘Zero’ means ‘no pain’ and ‘ten’ means ‘pain as bad as it could possibly be’. To ensure the safety of both NIBS techniques alone and their combination, an Adverse Effects Scale^33^ will be assessed. This scale consists of identifying the produced effects and measuring them on a scale from 1 to 4 points, being 1 – absent, 2 – mild, 3 – moderate and 4 – severe. The working memory task (n-back) will be applied after measurement of adverse effects.

All of the procedures described above will take place at the Institute of Psychiatry - HCFMUSP. However, after the end of the working memory task, the volunteers will be taken to the Nuclear Medicine Center - HCFMUSP, where the SPECT images will be acquired by a trained team.

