### Statistical analyses

Sample size was calculated using G*Power 3.1 software.^38^ Since this is an original study and no a-priori power analysis is provided, we estimate a moderate *f* – size effect (0.25). The analysis considered four groups, 4 measurements, correlation between repeated measures of 0.5, alpha of 0.05 and power of 0.85, resulting in a sample size of 28 participants. Considering possible losses, we estimate recruitment of 30 subjects (120 observations).

The Shapiro-Wilk test will be applied to identify the sample distribution. Assuming a normal sample, we will perform analysis of variance (ANOVA) having ‘group’ as independent variable and ‘area of activation’ (observed in the left DLPFC) as dependent variable. The Kruskal-Wallis test will be performed in case of a non-parametric sample. The SPECT images will be available in orthogonal cuts in the transverse, sagittal, and coronal planes (DICOM format). Images will be analyzed using the Statistical Parametric Mapping software (SPM12; Wellcome Department of Imaging Neuroscience, London, UK), executed in Matlab Version 2020 (MathWorks, Natick, MA). We will use SPM to form a statistical map according to the statistical threshold to identify differences among the groups. In-house scripts will be used for partial volume correction procedures based on structural MRI. The SPM images will be subtracted from each group to verify areas of functional activation.

ANOVA or its non-parametric extension will be applied for n-back and salivary cortisol, with ‘group’ as independent variable for both outcomes and ‘cortisol level’ (for salivary cortisol) and accuracy/response time (for working memory performance) as ‘dependent variables’. The associations between n-back task performance (accuracy and response time)/salivary cortisol level and cerebral activation will be estimated with linear regression. We will perform pathway analyses to verify whether cerebral activation is directly associated with the results of working memory performance and cortisol salivary level or is measured by these findings. We will also statistically investigate the possible learning effects of the repetitive application of the working memory task by grouping participants’ scores according to the chronological order of NIBS intervention assignments.

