The mood scales administered before each NIBS session (such as HAMD, BDI, PANAS, and HAI) will be used to investigate major mood oscillation between sessions. If significant mood changes (p < 0.05) are found, we will use these measures as potential moderators of the main outcomes of this study. Moreover, the VAS will be used to investigate any significant change in pain intensity before and after each session as well as between NIBS sessions. Finally, ANOVA will also be applied to investigate adverse effects (dependent variable) across groups (independent variable).

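### The cortisol analysis does not say which sample it uses and gives the pre-session sample no role, although the stated outcome is change

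*Protocol article*

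**What the plan says.** The Abstract (Methods) lists the outcomes, among them "accuracy and reaction time in the n-back task, and changes in salivary cortisol level", and states the sampling: "Salivary cortisol will be collected before and after each session". The Discussion restates the aim as finding out whether the protocols alter cortisol relative to sham.

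The Procedure section fixes both time points. Before stimulation: "Salivary cortisol will be collected after the motor threshold measurement and before venous access is obtained". After it, in the text below Figure 1: "VAS and salivary cortisol will be collected immediately after the end of the session".

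The Statistical analyses section gives the model: "ANOVA or its non-parametric extension will be applied for n-back and salivary cortisol, with ‘group’ as independent variable for both outcomes". The dependent variables follow: "cortisol level’ (for salivary cortisol) and accuracy/response time (for working memory performance". No change score, time term or pre-session covariate is mentioned. The linear regression and pathway analyses in the same section also refer to cortisol level without further definition.

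For pain, that section is explicit about the two time points: "the VAS will be used to investigate any significant change in pain intensity before and after each session".

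**The concern.** The outcome is a change and both samples needed for it are collected, but the written analysis names only a level. That level could be the post-session value, the change, or both samples together. These are different analyses with different precision, and the text leaves the choice open until after the data are seen.

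Two features make this more than shorthand. The pain analysis shows that the plan spells out before and after when it means to. And cortisol receives the same one-factor model as the n-back task, which by design has no pre-session measurement. Cortisol has one, and the model does not use it.

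What is at stake depends on the reading:

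- **Post-session value only.** Whatever a participant's cortisol was on arrival that day goes into the error term. With 30 people it can also fall unevenly across conditions by chance.
- **Pre and post samples pooled.** The pre samples cannot carry that session's stimulation effect, so the estimated effect shrinks.
- **Regression and pathway analyses.** Relating cortisol to cerebral activation is observational, so randomization of session order does not protect it. An undefined level mixes arrival cortisol with any response to stimulation.

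**Working it through.** **The plan's own figure.** Inputs from Statistical analyses: f = 0.25, four groups, m = 4 measurements, correlation between measurements ρ = 0.5, alpha 0.05, power 0.85, result 28. For a within-factor repeated-measures ANOVA (sphericity assumed), λ = f²·N·m/(1 − ρ), df1 = m − 1, df2 = (N − k)(m − 1). With k = 4 the smallest N is 27, which rounds up to 28 as a multiple of four. At N = 28, λ = 0.0625 × 28 × 4 / 0.5 = 14 and power is 0.878. The stated 28 is reproduced. It is not tied to cortisol, and nothing below alters it.

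**Set-up for cortisol.** Within a participant, across sessions, let the pre and post values vary with equal variance σ² and correlation r. The documents give no r, so it is an assumption shown over a range. Error variance for a condition contrast:

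- post-session value only: σ²
- change score: 2σ²(1 − r)
- post-session value adjusted for the same session's pre value: σ²(1 − r²), apart from one degree of freedom

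The change score beats post-only only if 2(1 − r) < 1, that is r > 0.5. Adjustment beats post-only for any non-zero r. It is never worse than the change score, because 2(1 − r) − (1 − r²) = (1 − r)² ≥ 0.

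**Numbers.** For power, assume that f = 0.25 applies to the post-session value, with N = 28, ρ = 0.5 and a true crossover (k = 1). λ is then 14 divided by the relative variance.

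| r | Change score: variance relative to post-only | Adjusted: variance relative to post-only | Power, post-only | Power, change score | Power, adjusted |
|---|---|---|---|---|---|
| 0.2 | 1.60 | 0.96 | 0.880 | 0.674 | 0.894 |
| 0.3 | 1.40 | 0.91 | 0.880 | 0.738 | 0.910 |
| 0.5 | 1.00 | 0.75 | 0.880 | 0.880 | 0.957 |
| 0.7 | 0.60 | 0.51 | 0.880 | 0.986 | 0.995 |

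In participants, post-only would need 1/0.75 = 1.33 times as many as the adjusted analysis at r = 0.5, and 1/0.51 = 1.96 times as many at r = 0.7. At r = 0.2 the factor is only 1/0.96 = 1.04.

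**Pooling.** If a condition shifts the post value by δ and leaves the pre value unchanged, the mean of the two samples shifts by (0 + δ)/2 = δ/2. The variance of that mean is σ²(1 + r)/2, which is 0.75σ² at r = 0.5. The standardized effect is then 0.5/√0.75 = 0.58 of the post-only one.

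**The case against.** The case for leaving the text alone has several parts.

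- **Level may be shorthand for change.** The Abstract and Discussion both speak of change, and the article never says that only the post-session sample is analysed. This stands: a reader might infer that the plan discards the pre-session sample, but the text leaves the variable undefined and does not say so.
- **The list of model terms is not complete.** The n-back section adds session order to the models, and mood scales may enter as moderators. A condensed article can leave covariates to the full plan. This weakens any inference from silence. It does not remove the mismatch, because the article does name the dependent and independent variables, and they do not match its own outcome.
- **A post-only contrast is not wrong.** A reader might infer that analysing a level fails to estimate the stated outcome, or biases it. For the comparison with sham the documents do not support that. Session order is randomized and counterbalanced, with a week between sessions, so arrival cortisol is equal in expectation across conditions unless there is carryover. The post-only contrast then has the same expected value as the contrast of changes. Chance imbalance is random error, not bias.
- **The remedy also uses a level.** True, but once the pre-session value is in the model, taking the post value or the change as dependent variable gives the same condition contrasts. The covariate is what matters.
- **The gain is not known.** Also true. At r = 0.2 it is 4%, and a raw change score would lose precision there.

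**Conclusion.** The point holds as a mismatch between the stated outcome and the written analysis. The cortisol variable is undefined, and a pre-stimulation sample taken in every session has no stated use. It does not hold as a claim of bias in the comparison with sham, nor as a claim that a post-only analysis has been prescribed.

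If the analysis were post-only, the avoidable error variance relative to baseline adjustment is r²: from 4% to 49% for r between 0.2 and 0.7. This rests on an assumed r, equal pre and post variances, and a within-subject analysis such as the sample size calculation supposes. The power figures also need f = 0.25 to apply to post-session cortisol, which the article does not state.

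The point is worth correcting because cortisol is one of three outcome domains and the data needed are already planned. It does not threaten the trial as a whole.

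**What to change.** In Statistical analyses, replace the undefined level by a definition: post-session salivary cortisol is the dependent variable, and the same session's pre-stimulation cortisol is a covariate in the within-subject model. State that this is how change is assessed, so that the section agrees with the Abstract and Discussion. Do not rely on a simple change score, which is less precise than the post value alone if r is below 0.5. Do not enter pre and post samples together as one undifferentiated level.

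Carry the same definition into the linear regression and pathway analyses, so that they relate cerebral activation to cortisol adjusted for its value on arrival.

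A log scale, the participant's mean pre-stimulation cortisol as a further covariate, and reporting of adjusted ratios are optional refinements. The cost is wording and one degree of freedom, with no new samples or visits.

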## Material and methods

### Design

We propose a phase-I, randomized, double-blind, within-subjects, full-factorial study design, which is efficient for testing the standalone and combined effects of tDCS and iTBS.

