## Discussion

This study will be a phase-I trial designed to assess the combined and standalone effects of the tDCS and iTBS interventions over the PFC using multimodal assessments, comprising neuroimaging, cognitive tests, and salivary cortisol measures, which will be essential to evaluate the effects of concomitant NIBS administration, as well as to enhance knowledge regarding the effects of individual application of the techniques.

Considering the previous studies investigating the effects of two NIBS interventions^20 , 21 , 39^ and neuroimaging studies evaluating the online effects of tDCS over the DLPFC (17 subjects for two groups, with a total of 34 observations),^40^ our study presents the largest sample recruited to date. Besides, the within-subject full-factorial design will allow us to analyze a total of 120 observations. This sample decreases the chances of type I and type II errors, compared to previous studies.

Regarding the combined protocol adopted in our study, although application of dual facilitatory protocol stimulation can increase the chance of provoking homeostatic plasticity effects,^21^ this approach was chosen since previous studies have shown that induction of both LTP (long-term potentiation) or LTD (long-term depression) by burst stimulation depends on the membrane potential of the postsynaptic neurons and that the effects of stimulation can be modified by external hyper/depolarization.^20 , 41^ Besides, according to the literature, tDCS effects are improved by a concept known as ‘functional targeting,’^17^ in which neuronal networks that are already activated might be more stimulated compared to non-primed ones. Following these findings, the rationale behind the concurrent application of tDCS and iTBS is that DC current will probably bias iTBS effects.^20^ Moreover, it is important to underscore that the protocol for this study is slightly different from the ‘priming’ protocols of the previous studies with TMS,^42^ since here the stimulation protocols will be applied concomitantly and both NIBS protocols are associated with neuronal facilitation.

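### The regression of n-back and cortisol on perfusion names no participant term; if the 120 repeated rows are pooled, its false-positive rate would be about 14% at the plan's own correlation

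*Protocol article*

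**What the plan says.** The Design section sets the structure: "We propose a phase-I, randomized, double-blind, within-subjects, full-factorial study design". Every participant has all four sessions, and Statistical analyses gives the count: "we estimate recruitment of 30 subjects (120 observations". The sample-size calculation in that section assumes "correlation between repeated measures of 0.5, alpha of 0.05 and power of 0.85".

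For the link between outcomes, the same section states: "The associations between n-back task performance (accuracy and response time)/salivary cortisol level and cerebral activation will be estimated with linear regression". It adds a path analysis to "verify whether cerebral activation is directly associated with the results of working memory performance and cortisol salivary level or is measured by these findings".

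The Discussion says that "the within-subject full-factorial design will allow us to analyze a total of 120 observations", and that this sample lowers both type I and type II error compared with earlier studies.

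On timing, Procedure says: "The radiotracer (99mTC-ECD) will be injected right after the start of the iTBS protocol". The text after Figure 1 places the second saliva sample immediately after stimulation and then says: "The working memory task (n-back) will be applied after measurement of adverse effects".

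**The concern.** Four sessions from one person are not four independent observations. A linear regression over 120 rows with no participant term treats them as if they were, and its standard error is too small whenever both variables are correlated within person. The slope also answers a mixed question. Some people may have both higher perfusion and better scores at every session, and a pooled slope picks that up together with any change that stimulation brings about. The Discussion wants to compare cortisol and working memory with brain activity across the stimulation protocols, which is a within-person question. At stake is whether a reported link between perfusion and cognition or cortisol can be read as something that moves with stimulation.

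The path-analysis sentence raises a separate issue. As printed, *measured* has no workable meaning there. One reading places n-back and post-session cortisol upstream of a perfusion signal that was fixed before either was collected.

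**Working it through.** **1. The plan's own figure.** Inputs from Statistical analyses: f = 0.25, m = 4 measurements, k = 4 groups, correlation 0.5, alpha 0.05, power 0.85. For the within-factors repeated-measures F test:

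- λ = f² × N × m / (1 − ρ) = 0.0625 × 28 × 4 / 0.5 = 14
- df = (m − 1, (N − k)(m − 1)) = (3, 72)
- power at N = 28: 0.878

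The smallest N reaching 0.85 is 27, or 28 as a multiple of four, so the stated 28 reproduces. This calculation treats the sessions as correlated at 0.5. The article gives no error rate for the regression.

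**2. Pooled regression with no true association.** Take 30 people × 4 sessions, within-person correlations ρx and ρy, and participant effects in the two variables independent of each other. The variance of the slope is inflated by

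DE = 1 + (m − 1) × ρx × ρy,

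and the actual size of a two-sided 5% test is about 2 × [1 − Φ(1.96 / √DE)].

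At ρx = ρy = 0.5: DE = 1 + 3 × 0.25 = 1.75, √DE = 1.32, 1.96 / 1.32 = 1.48, so the size is 13.8%. The 120 rows then carry the information of about 120 / 1.75 ≈ 69 independent ones for this slope.

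Simulation used 20,000 replicates. All correlations other than 0.5 are assumptions.

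| ρx / ρy | DE | Formula | Simulated, pooled | Simulated, participant + condition terms |
|---|---|---|---|---|
| 0 / 0.5 | 1.00 | 5.0% | 4.8% | 4.7% |
| 0.3 / 0.3 | 1.27 | 8.2% | 8.3% | 5.0% |
| 0.5 / 0.5 | 1.75 | 13.8% | 13.5% | 5.0% |
| 0.5 / 0.8 | 2.20 | 18.6% | 18.9% | 4.8% |
| 0.7 / 0.7 | 2.47 | 21.2% | 21.4% | 5.0% |
| 0.8 / 0.8 | 2.92 | 25.1% | 25.8% | 5.0% |

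A separate run of 10,000 replicates gave 8.4%, 14.0% and 21.6% at 0.3, 0.5 and 0.7.

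**3. Other forms of the regression.** Run on one session (n = 30) or on participant means, the simulated rate is about 5% in every row of the table.

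**4. Is a participant term enough?** Suppose the conditions shift both variables by f = 0.25 with no person-level link, at correlation 0.5. Pooled regression then rejects 17.5%, pooled regression with condition 13.9%, participant effects without condition 26.9%, and both terms together 5.2%. Both terms are needed if the slope is to mean more than both variables responding to the same condition.

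**5. Time order.** The sequence in Procedure is: first saliva sample, tracer injection at the start of iTBS, end of stimulation, second saliva sample, adverse-effects scale, n-back, scan. The Discussion describes SPECT as an online measure of perfusion under stimulation, so by the article's own account the signal belongs to the injection, not to the later scan. Post-session cortisol and n-back therefore follow it, while pre-session cortisol precedes it. Reversing an arrow in the path model changes what a coefficient can mean. It does not change the type I error computed above.

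**The case against.** The article never says that the rows are pooled. It names linear regression and stops, and as a condensed account it may leave model terms to a fuller plan. Other wording fits other readings. The n-back section takes performance after sham as the reference and allows negative response times, which suggests difference scores. The Discussion speaks of comparing the measures with brain activity in the different protocols, which suggests one regression per protocol at n = 30, where 5% holds. The 0.5 is a planning value for the ANOVA, not a measured correlation for perfusion, accuracy, response time and cortisol.

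Most of this stands, and it makes the error rate conditional. It does not remove the point. The article names a model without a participant term and presents the 120 observations as protection against type I error. Differences from sham would cancel stable person effects, but a person's three differences share one sham session and remain clustered. A per-session regression keeps its size but does not isolate within-person change.

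A reader might also infer that false positives could reach 40 to 59%. Those figures come from simulating a true between-person correlation of 0.3 with no within-person relation, at correlations of 0.5 and 0.7. The plan's stated target is associations in general, so finding a real between-person association is not a false positive for it. The figures show only how easily a pooled slope could be misread as within-person change.

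A reader might further infer that the plan fits a path in which later measures explain an earlier one. That rests on reading *measured* as *mediated*, with activation as the outcome. The sentence fits equally well a path from activation through post-session cortisol to n-back, which is in the correct order.

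**Conclusion.** The concern holds in conditional form. If the regression pools all 120 rows, as the Discussion's count suggests, and both variables have the plan's own correlation of 0.5, a nominal 5% test has a true size of about 14%, nearly three times nominal. The size depends on that correlation: about 8% at 0.3, 21 to 22% at 0.7, and near 5% if either variable is uncorrelated within person. The documents do not support a flat statement that the rates will exceed 5%, because pooling is inferred and a per-session or participant-mean regression would keep its size.

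The path-analysis wording is a separate and smaller defect. It needs clarifying, and if mediation is meant the order must respect the timing of the tracer. It has no bearing on the 14%.

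Both are supporting analyses. The comparisons of perfusion, n-back and cortisol across conditions, which address the main hypothesis, are not affected by this point.

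**What to change.** Replace the regression sentence with a model that carries both participant and condition. One option is a mixed model with a random participant intercept in which perfusion is split into the participant's mean and the session's deviation from it. The other is a participant fixed-effects regression. State that claims about stimulation-related change rest on the within-person perfusion slope, and report any between-person slope separately and label it as such. In the Discussion, do not credit the 120 observations with lower type I error unless the clustering is modelled.

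In the path-analysis sentence, say what *measured* means. If it is *mediated*, specify stimulation, then perfusion, then post-session cortisol and n-back, using a method suited to within-subject data, and say which cortisol sample enters.

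The cost is a few lines of text and slightly more programming. The data, visits and sample size do not change. The fixed-effects version leaves 120 − 30 − 3 − 1 = 86 residual degrees of freedom, against 118 for the pooled slope.

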### Procedure

At the beginning of the study, participants will be screened for participation and asked to give written informed consent. The study is in accordance with the Declaration of Helsinki and was approved by the Ethics Committee at the São Paulo University Hospital das Clínicas (HCFMUSP) and registered on the Plataforma Brasil database (CAAE: 89310918.8.0000.0068).

Participants will be randomized in accordance with a computer-generated list at www.randomizer.org and allocation will be conducted by an assistant not involved in the project. Participants will be asked to come to the research center five times. In line with previous studies of (non)combined NIBS protocols, there will be a one-week interval between the sessions to ensure elimination of carryover effects.^20^ On the first day, all participants will undergo a 3 Tesla MRI (GE, 750W system integrated within a 3.0 Tesla General Electric PET/MRI scanner) scan during which we will acquire T1-weighted and T2-weighted sequences (repetition time [RT] = 1900 ms, echo time [ET] = 2.2 ms, flip angle = 9°, 176 slices/volume, slice thickness = 0.8 mm). MRI acquisition is performed beforehand to target the right and left DLPFC via a neuronavigation system (Brainsight, Rogue Resolutions, Inc). Both left and right DLPFC will be located in each participant by reverse coregistration from the MNI152 stereotaxic coordinates (x - 38, y + 44, z + 26 and x + 38, y + 44, z + 26, respectively) and marked on a cap. This method has been identified as optimal on the basis of clinical outcomes and whole brain functional connectivity.^30 , 31^ After neuronavigation, all other sessions will take place in a well-controlled laboratory environment at the Institute of Psychiatry - HCFMUSP, São Paulo, Brazil. The same procedures will be applied in each of the four sessions, except for neuronavigation, which will only be conducted during the first session.

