### Working memory (n-back) task

The n-back will be programmed in E-prime 2.0 software (Psychology Software, Tools Inc Pittsburgh, Pennsylvania, USA). Images will be presented on a 15-inch LCD computer screen and participants will be seated at a distance of approximately 50 cm from the screen. The visual stimulus consists of letters of the alphabet (A to Z) that will appear individually and randomly on the computer screen. Two conditions will be applied, 0-back and 2-back. The tasks will present 3 blocks of 30 letters, each one being displayed on the screen for 500ms, with an interstimulus interval of 3000 ms. A correct response occurs when the subject identifies letter ‘X’ (0-back task) and the same stimuli presented two positions before (2-back task). Response time will also be measured. Higher accuracy values will represent improvement, whereas lower (including negative) response times will represent faster response. This is the same protocol previously used by our group.^8 , 36^

Finally, the n-back task will not be applied before the NIBS session to avoid learning effects. Moreover, n-back performance after the sham protocol will be used as the reference value in our statistical comparison and the randomized and counter-balanced NIBS protocols will allow us to statistically evaluate learning effects by introducing order as a variable in our statistical models. This methodology was applied based on previous studies evaluating working memory performance with NIBS intervention.^37^

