### Limitations

First, we will not compare the effect of iTBS and cathodal tDCS that have also been shown to increase cortical excitability.^21^ Second, some technical limitations regarding the SPECT exam should be underscored: 1) SPECT measures the CBF, which does not generally exactly reflect brain metabolism, being a better surrogate for brain activity compared with cerebral perfusion; 2) although SPECT is a consolidated neuroimaging method, it presents poorer contrast and spatial resolution when compared to Positron Emission Tomography (PET), for instance; and 3) the within-subject design may introduce learning effects in working memory tasks.

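### Session order is promised as a model variable for the n-back task, but the stated ANOVAs contain only group, so a practice trend would stay in the error term of the treatment comparison

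*Protocol article*

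**What the plan says.** Two sections of the protocol article describe how session order is handled.

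- **Working memory (n-back) task.** The task is not given before stimulation, and performance after sham is the reference. The section relies on "the randomized and counter-balanced NIBS protocols", which it says will "allow us to statistically evaluate learning effects by introducing order as a variable in our statistical models".
- **Statistical analyses.** The SPECT ANOVA is described as "having ‘group’ as independent variable and ‘area of activation" as dependent variable. The n-back and cortisol ANOVAs are described "with ‘group’ as independent variable for both outcomes". Neither description has an order or session term. Learning is then treated in a sentence of its own, for working memory only: the plan will investigate "possible learning effects of the repetitive application of the working memory task by grouping" participants' scores by the chronological order of the sessions.

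The Limitations section accepts that "the within-subject design may introduce learning effects in working memory tasks". On how orders are generated, the Procedure section says only: "Participants will be randomized in accordance with a computer-generated list at www.randomizer.org".

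**The concern.** The n-back section describes an adjustment, with order in the model. The Statistical analyses section describes a separate check, with scores regrouped by order. These are different analyses. A regrouping shows whether scores improve from session 1 to session 4, but leaves that improvement inside the comparison of conditions.

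This matters most for n-back. Without a pre-session score, each person's result under active stimulation is compared directly with the same person's result under sham, one to three weeks earlier or later. Practice between those visits goes into the within-participant residual. Any difference in average session position between two conditions in the realised list also goes into the contrast. The plan itself expects practice: it omits the pre-session task to avoid learning and lists learning as a limitation.

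**Working it through.** **Inputs.** From Statistical analyses: f = 0.25, 4 groups, 4 measurements, correlation 0.5, alpha 0.05, target power 0.85, 28 participants required, 30 recruited. Assumed, because the documents give no figure: a linear practice trend totalling T within-participant SD from session 1 to session 4. Participant is taken to be in the model, as the sample-size calculation implies.

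**1. The plan's own figure.** For a within-factor repeated-measures ANOVA, lambda = f² × N × m / (1 − rho), with df 3 and (N − 4) × 3.
- At N = 28, lambda = 0.0625 × 28 × 4 / 0.5 = 14, df 3 and 72, power 0.878.
- The smallest N reaching 0.85 is 27, which rounds to 28 for four equal groups.
- At N = 30, power is 0.902.

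The stated 28 reproduces and is not in dispute. The calculation contains no practice trend.

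**2. Residual variance when session is left out.** Positions 1 to 4 have squared deviations from their mean of 2.25 + 0.25 + 0.25 + 2.25 = 5 per participant. These fall on 3 within-participant degrees of freedom, so the variance per degree of freedom is 5/3. The slope is T/3 per session. With random orders, the residual variance is multiplied by 1 + (5/3)(T/3)², and lambda is divided by the same factor.

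| Trend T (within-participant SD) | Residual variance | lambda (N = 28) | Omnibus power |
|---|---|---|---|
| 0 | 1.000 | 14.0 | 0.878 |
| 0.5 | 1.046 | 13.4 | 0.861 |
| 1 | 1.185 | 11.8 | 0.811 |
| 2 | 1.741 | 8.0 | 0.630 |

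A simulation of 28 participants (20,000 runs per case) gave residual mean squares of 1.19 and 1.74 and power of 0.815 and 0.633 for T = 1 and 2. With no treatment effect, rejection was 0.052 and 0.050. Mean bias was about zero.

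**3. Does the session term recover the loss?** A second simulation used 30 participants and 4,000 runs per case, with drift in total SD per session. One within-participant SD is √0.5 = 0.707 total SD, so T = 1 is 0.236 per session and T = 2 is 0.471.

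| Drift per session | Random orders, no term | Random orders, with term | Near-balanced, no term | Near-balanced, with term |
|---|---|---|---|---|
| 0 | 0.905 | 0.888 | 0.896 | 0.908 |
| 0.1 | 0.894 | 0.887 | 0.900 | 0.902 |
| 0.2 | 0.860 | 0.899 | 0.874 | 0.910 |
| 0.3 | 0.797 | 0.888 | 0.818 | 0.907 |
| 0.5 | 0.647 | 0.891 | 0.603 | 0.895 |

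The term holds power near 0.90 throughout. Near-balanced means four Williams-type sequences with 28 of the 30 people exactly balanced. Balance alone does not rescue the group-only model. The treatment contrasts are then almost free of the trend, but the error term still contains it. Type I error falls to 0.028, 0.016 and 0.004 at drifts of 0.2, 0.3 and 0.5, so the test becomes too conservative.

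**4. Cost of the term with random orders.** Power with the term averages (0.888 + 0.887 + 0.899 + 0.888 + 0.891) / 5 = 0.891. The formula with one group, no trend and no term gives 0.904 at N = 30. The cost is about one point.

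**5. Chance imbalance, only if each order is drawn independently.** One position has variance 1.25. The difference of two positions in one random order has variance 2 × 1.25 + 2 × 1.25/3 = 3.33. Over 30 people the SD is √(3.33/30) = 0.33 session, with 95% within about ±0.67. At T = 1 (slope 1/3) that is a shift with SD 0.11 and a 95% limit of about 0.22 within-participant SD. It centres on zero and is already counted in the variance in step 2.

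**The case against.** The best defence is that the two sections can be read together. The n-back section commits to order in the models, while the Statistical analyses section summarises the ANOVAs without saying that group is the only term, and then adds a learning analysis. On that reading order is not ignored and only the wording needs aligning. This stands in part: order is considered for n-back. But the section that defines the models does not carry the commitment and describes a different procedure, and the one non-parametric fallback it names, Kruskal-Wallis, is a one-factor test that cannot hold a session term.

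A second defence is that the practice sizes are hypothetical. That is correct. At a drift of 0.1 total SD per session the loss is about one point (0.905 to 0.894), which is negligible.

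A reader might go further on three points that the documents do not support.

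- *The randomisation list fails to deliver counterbalancing.* This is not shown. Counterbalancing is stated, and a computer-generated list can assign people to a balanced set of sequences. An article may leave the sequence set to the full protocol. Thirty is not a multiple of four, but nothing claims exact balance at 30, and 28 is a multiple of four.
- *An order term was also promised for SPECT and cortisol.* It was not. The learning concern is confined to n-back, and the documents give no evidence of habituation in the other outcomes.
- *Results will be biased or falsely positive.* Random ordering protects against that. Any shift is chance imbalance in one realised list.

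**Conclusion.** The point holds as an inconsistency with a cost in precision. The article promises order in the models for n-back, states ANOVAs without it, and substitutes a separate check that does not adjust the treatment comparison.

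The size depends on a practice trend that the documents do not give. If it is linear and totals 1 within-participant SD over four sessions, omnibus power falls from 0.88 to about 0.81, below the planned 0.85. At 2 SD it falls to about 0.63, and at 0.5 SD it stays at 0.86. These figures assume random orders, 28 analysed participants, the plan's f and correlation, and participant in the model. Validity is not threatened, and the sample-size figure is not wrong. The change is worth making because it is cheap and helps whether orders are random or balanced.

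**What to change.** Reconcile the n-back section with the Statistical analyses section. For n-back accuracy and response time, state a repeated-measures model with condition, session number (1 to 4, categorical) and participant, and keep the regrouping by chronological order as a description only. If normality fails, choose a fallback that can also carry participant and session.

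Add the same session term to the SPECT and cortisol models, described as a precision gain and not as the correction of a broken promise.

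The cost is three degrees of freedom per model and about one point of power if there is no trend. The randomisation need not change, and the term can be added after enrolment has begun, provided that it is fixed before unblinding.
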